#### Secondary outcomes

2.6.2

The secondary outcomes are clinical cure at the end of therapy, TB-recurrence rate of spinal tuberculosis 12 months after completion of treatment, the proportion of participants who are culture negative at 8 weeks, the proportion of discontinuation of assigned treatment for a reason other than microbiological ineligibility, the incidence of AEs, the proportion of participants who have residual neurological dysfunction, and pharmacokinetic (PK) parameters and pharmacodynamic (PD) target attainment rate of the anti-TB drugs (Asin-Prieto et al., 2015; Verbeeck et al., 2016; Zuur et al., 2018). The determination of clinical cure needs to be based on a composite of clinical, laboratory (normal complete blood count and erythrocyte sedimentation rate), and radiological factors. Clinically, patients are considered “healed” at the end of therapy if they show marked improvement in spinal symptoms, including pain, tenderness, and paraspinal muscle spasm, along with a return to their pre-disease functional status, weight gain, and absence of residual instability or neurological deficits. Radiologically, healing is defined as substantial regression of epidural or paraspinal abscess/granulation tissue, marrow reconversion, and fatty reconstitution of the affected bone at the final follow-up (Nene et al., 2019). For PK parameters and PD target attainment rate, plasma concentrations of rifapentine and moxifloxacin are measured via validated liquid chromatography-tandem mass spectrometry (LC-MS/MS) from 2-4 blood samples collected per participant (Weeks 2, 4, 8). PK parameters (area under the concentration-time curve over 24 h [AUC_0–24h_]; maximum plasma concentration [C_max_]) are calculated using the NONMEM 7.4 software. PD targets (rifapentine: AUC_0–24h_/minimum inhibitory concentration [MIC] (Verbeeck et al., 2016; Zuur et al., 2018); moxifloxacin: AUC_0-24h_/MIC (Asin-Prieto et al., 2015) are based on anti-TB pharmacology; the attainment rate is the proportion of participants meeting both targets.

### Sample size

2.7

We estimated the sample size based on the non-inferiority hypothesis that the TB-recurrence rate of spinal tuberculosis at 24 months after completion of treatment of the short-course regimen will be no worse than the empirical long-course regimen. It is assumed that the TB-recurrence rate in the empirical long-course group is 5% and the rate will be the same in the short-course regimen arm. Considering a 10% dropout rate, a sample size of 150 per arm (300 in total) will give 80% power (one-sided type I error of 5%) to demonstrate a 6.6% non-inferiority margin (Dorman et al., 2021) using Pearson chi-square test with normal approximation. Detailed sample size calculation steps, including the statistical formula, parameter justification, and sensitivity analysis results, are provided in the Supplementary Material.

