### Randomization

2.3

A blocked randomization approach with stratification will be employed to allocate eligible patients into the short-course regimen [6-month anti-TB regimen] group and the empirical long-course regimen [12-month anti-TB regimen] group in a 1:1 ratio. The participants will be stratified according to the study sites. All research staff will undergo uniform training to ensure consistency across all study sites. The randomization list will be generated using SAS v9.4, and the allocation sequence will be carried out by the trial statistician via the central phone system. Both participants and investigators will be aware of the allocation, as the study will not be blinded.

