### Statistical analysis

2.9

The statistical analyses will be carried out in SAS v9.4 by independent statisticians. Descriptive statistical analysis will be performed by calculating the mean ± SD, median (minimum-maximum, or lower quartile-upper quartile) for continuous variables and counts (percentages) for categorical variables. The statisticians will perform chi-square test or Fisher’s exact test for categorical variables and Student’s test or Wilcoxon rank sum test for continuous variables. It will be considered statistically significant if p value <0.05. The efficacy analysis will use intention-to-treat, per-protocol, and as-treated populations. The concentration of anti-TB drugs will be determined using a validated LC-MS method at the Center for Pharmaceutical Analysis and Testing, School of Pharmaceutical Sciences, Shandong University. NONMEM 7.4 will be used to determine whether the PD targets have been achieved for each participant. Detailed statistical analyses are provided in the Supplementary Material.

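### The sample-size method does not deliver 5% error and 80% power together: with about 7 events per arm the normal-approximation margin test runs at 5.9%, and a score test that holds about 5% has about 76% power

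*Protocol article*

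**What the plan says.** The Sample size section of the protocol article sets a non-inferiority hypothesis for recurrence at 24 months after the end of treatment. Its assumptions are:

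- Control rate: "TB-recurrence rate in the empirical long-course group is 5" per cent.
- No true difference: "the rate will be the same in the short-course regimen arm".
- Margin: the trial is sized "to demonstrate a 6.6% non-inferiority margin".
- Error and power: "one-sided type I error of 5" per cent, and 150 per arm "will give 80% power" after allowing for 10% dropout.
- Method: "using Pearson chi-square test with normal approximation".

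The Statistical analysis section names chi-square and Fisher's exact tests for categorical data in general, with one threshold: "It will be considered statistically significant if p value <0.05". It gives no side for that p value, no confidence limit and no reference to the margin. It does not single out the primary endpoint, and it sends the reader to the Supplementary Material for detail. The Randomization section adds: "The participants will be stratified according to the study sites".

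**The concern.** A normal approximation to a difference in proportions is weakest when events are few. Here the expected count is 135 × 0.05 = 6.75 per arm. If the approximate test exceeds its nominal error, the stated power is partly bought with that excess, and a test that keeps to 5% has less.

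A second matter concerns how the result is read. Chi-square and Fisher's tests, as ordinarily run, test whether two rates are equal. They do not test whether the short course is worse by less than 6.6 points. A reader who has only the Statistical analysis section could take a non-significant result as support for non-inferiority. At stake is a claim that would halve treatment from 12 to 6 months.

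**Working it through.** **Inputs.** Recurrence 5% in both arms, margin 0.066, one-sided α = 0.05, power 80%, dropout 10%, 1:1 allocation (Sample size and Randomization sections).

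**1. The plan's own figure.** Unpooled normal approximation:

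n = (z₀.₉₅ + z₀.₈₀)² × [p₁(1 − p₁) + p₀(1 − p₀)] / margin²

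= (1.6449 + 0.8416)² × (2 × 0.05 × 0.95) / 0.066² = 6.183 × 0.095 / 0.004356 = 134.8, so 135 evaluable.

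135 / 0.90 = 150 per arm. The stated size is reproduced.

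**2. Exact behaviour at 135 evaluable per arm.** For every pair of event counts, decide whether the test declares non-inferiority, then add up the binomial probabilities. Type I error takes the short-course rate at the control rate plus 6.6 points. Power takes 5% in both arms.

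- Normal-approximation (Wald) test: z = (p̂_short − p̂_long − 0.066) / SE, with SE from the observed rates.
- Farrington-Manning score test: the same numerator, with SE from the rates estimated under the constraint that they differ by 0.066.

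| Test (one-sided 5%) | Error, control 5% | Error, control 3% | Error, control 2% | Power |
|---|---|---|---|---|
| Normal approximation | 5.9% | 6.5% | 6.9% | 80.5% |
| Farrington-Manning score | 5.0% | 4.8% | 4.5% | 75.9% |

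Using a pooled variance in the normal-approximation test gives the same figures at this size.

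**3. Sensitivity to the number evaluable.** With all 150 per arm evaluable, the score test has 79.8% power and 4.9% error at the planning rate, and the normal-approximation test has 83.0% power and 5.6% error. Event counts are discrete, so power moves unevenly with n: the score test has 74.6% at 134 and 75.7% at 136. It stays at or above 80% from 154 evaluable, and 154 / 0.90 = 171.1, so 172 per arm.

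**4. Cross-check by the asymptotic score formula.** At 5% in both arms the constrained rates are 0.0987 and 0.0327, so the null SD term is √(0.0987 × 0.9013 + 0.0327 × 0.9673) = 0.347. The SD term under the alternative is √0.095 = 0.308. Power = Φ[(0.066 × √135 − 1.645 × 0.347) / 0.308] = 73.7%. This is a little below the exact 75.9% and points the same way.

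**5. The equality test read as non-inferiority.** At true rates of 11.6% and 5% with 135 per arm, an ordinary two-sided chi-square test at 5% is non-significant in 48.6% of trials. A non-inferiority test should pass a regimen at the margin about 5% of the time.

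**6. Site.** In simulation with 14 near-equal sites and an assumed between-site SD of the recurrence rate of 0, 3 or 5 points, the unstratified normal-approximation test has error of 5.9%, 5.7% and 5.7%. Leaving site out does not raise the error.

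**The case against.** The 150 per arm contains no arithmetic error, and 80% power does hold for the method named (80.5% exact). The 76% appears only after a different test is substituted, and it assumes that the full 10% is lost. At the planning rate the excess error is 0.9 points; the larger figures need control rates below the assumed 5%. All of this stands. It does not remove the point that the 80% belongs to a test whose error is above 5%.

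Three stronger readings are tempting, and the document does not support them.

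- *That the primary comparison will be decided by a chi-square or Fisher test of equality.* The sentence on tests is general, the Sample size section ties recurrence to a margin, and the detailed analysis is placed in a supplement that is not shown. The 49% therefore describes a misreading to be ruled out, not a rule that the protocol states.
- *That p<0.05 contradicts the one-sided 5% used for sizing.* No side is given, and a one-sided margin test at p<0.05 is exactly the sizing rule. Only if the threshold were two-sided (one-sided 2.5%) would power by the plan's formula fall to 70.1%.
- *That leaving out the site strata breaks the error rate.* The article is merely silent on adjustment for site, and step 6 shows that the error does not rise.

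**Conclusion.** The point holds in limited form. The stated pair of one-sided 5% error and 80% power is not delivered by one and the same test. The normal-approximation margin test has about 80% power at a true error of 5.9%; a score test that holds about 5% has about 76% power. The shortfall is about 4 points of power, or 0.9 points of error, and the excess error grows if control recurrence is below 5%.

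These figures assume 5% recurrence in both arms, 135 evaluable per arm and independent binomial outcomes. With no dropout the score test reaches 79.8%.

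The visible analysis text names only equality tests. Whether the supplement holds a correct margin rule cannot be judged from the article, so the request there is to state the rule.

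**What to change.** State one decision rule for recurrence: the short course is non-inferior if the upper limit of the score interval for the risk difference (short minus long) is below 6.6 points, at the one-sided 5% level used for sizing. Name one method, Miettinen-Nurminen or Farrington-Manning. Restate power as about 76% with 10% dropout. Keep two-sided chi-square and Fisher tests for superiority and descriptive comparisons, and say that a non-significant equality test is not evidence of non-inferiority.

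As a secondary improvement, stratify the interval by site with Mantel-Haenszel weights, to match the randomisation. This is not needed to control the error and adds little or no power. In a simulation of 40,000 trials with 14 near-equal sites and no site variation, the stratified score test had 76.3% power and 5.3% error without the Miettinen-Nurminen variance correction, and 74.8% and 4.9% with it. That difference is a further reason to name the exact version.

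The cost is wording in the analysis plan and standard SAS code, with no extra patients. Stated power falls by about 4 points. Restoring 80% under the score test would be a separate decision: about 172 per arm, 344 in total.

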### Management of loss to follow-up (LTFU)

2.8

To mitigate LTFU risks during the 36-month follow-up, high-risk participants (e.g., those with unstable residence or long distance from study sites) are required to provide alternative contacts (Li et al., 2023), while dedicated coordinators use a tiered reminder system (phone, SMS/WeChat) to notify participants of scheduled follow-up visits; within 48 h of a missed visit, additional contact attempts are made via primary and alternative channels, and a 10% LTFU allowance has been incorporated into the sample size calculation (150 participants per arm) to ensure 80% statistical power for the primary outcomes (Ren et al., 2016; Li et al., 2023).

### Statistical analysis

2.9

The statistical analyses will be carried out in SAS v9.4 by independent statisticians. Descriptive statistical analysis will be performed by calculating the mean ± SD, median (minimum-maximum, or lower quartile-upper quartile) for continuous variables and counts (percentages) for categorical variables. The statisticians will perform chi-square test or Fisher’s exact test for categorical variables and Student’s test or Wilcoxon rank sum test for continuous variables. It will be considered statistically significant if p value <0.05. The efficacy analysis will use intention-to-treat, per-protocol, and as-treated populations. The concentration of anti-TB drugs will be determined using a validated LC-MS method at the Center for Pharmaceutical Analysis and Testing, School of Pharmaceutical Sciences, Shandong University. NONMEM 7.4 will be used to determine whether the PD targets have been achieved for each participant. Detailed statistical analyses are provided in the Supplementary Material.

### Safety and AEs monitoring

2.10

All AEs will be precisely monitored and recorded from the moment of obtaining informed consent to the follow-up visit. Serious AEs will be reported according to the local regulations and procedures.

The safety monitoring committee of this trial consists of [name] [name] from the Shandong University and [name] from Paris Cité University. And the data monitoring will be performed by Institute of Clinical Pharmacology, Shandong University. The monitoring will be in accordance with the requirements of the GCP guidelines.

## Discussion

3

Spinal tuberculosis is a bone infection caused by *Mycobacterium tuberculosis* (Mtb), located in deep tissues, and its treatment currently faces multiple challenges. From a pharmacological perspective, bone tissue is often poorly vascularized, resulting in inadequate drug penetration. For example, the bone concentration of rifampin is only 20%–40% of its plasma concentration (Thabit et al., 2019). From a bacterial perspective, the formation of Mtb biofilms has been confirmed *in vitro*, in animal infection models (in the bone) and in patients (in the lungs) (Trivedi et al., 2016; Chakraborty et al., 2021; Staats et al., 2021). Biofilm formation contributes to the development of drug resistance. Furthermore, Mtb can evade immune responses by inhibiting macrophage maturation, lysosomal acidification, and suppressing oxidative stress, apoptosis, and autophagy, allowing the bacteria to remain dormant within the host (Zhai et al., 2019). This persistence of bacteria makes clinical relapse more likely. Therefore, the bacteria responsible for spinal tuberculosis are particularly difficult to fully eradicate, which is why treatment often requires a prolonged duration (12–18 months). However, the contradiction arises in that the toxicity of the drugs and the patients’ adherence issues, etc. During such long treatments may lead to interruptions, undermining the very success of the therapy. This is the core dilemma in treating spinal tuberculosis.

Therefore, shortening the treatment duration has become a key strategy, with related studies already conducted on non-tuberculous osteoarticular infections (such as prosthetic joint infections and osteomyelitis) (Yen et al., 2019; Benavent et al., 2021; Scheper et al., 2022). For pulmonary tuberculosis, a 4-month treatment regimen also has been proven to be non-inferior to a 6-month regimen (Dorman et al., 2021). Shortening the treatment duration for spinal tuberculosis may be achievable, and the key lies in selecting the right drugs that can address the challenges in treating spinal tuberculosis. The anti-tuberculosis efficacy of rifapentine and moxifloxacin has been confirmed in a 4-month regimen for pulmonary tuberculosis (Dorman et al., 2021). Moreover, animal data on rifapentine show that, at the same dosing levels as rifampin, rifapentine achieves higher concentrations than rifampin in bone, except in the medulla (Iversen et al., 1983). Additionally in an osteoblast infection model, the minimum biofilm eradication concentration of rifapentine for *S. aureus* isolates is lower than that of rifampin (Abad et al., 2020). Moxifloxacin also exhibits good penetration into bone and joints (Malincarne et al., 2006). Rifapentine demonstrates significantly lower hepatotoxicity compared to rifampin (Dorman et al., 2021) and moxifloxacin demonstrates comparable tolerability to ethambutol, a medication widely regarded as having a high safety profile (Conde et al., 2009). Therefore, we hope to shorten the treatment duration to 6 months by replacing the drugs in the anti-tuberculosis regimen with rifapentine and moxifloxacin.

Finally, conducting this study in China is highly feasible and of great significance, as China ranks third among the 30 countries with the highest TB burden in WHO data (WHO, 2024). Among the various forms of extrapulmonary tuberculosis, spinal tuberculosis is the most prevalent, constituting roughly 1%–3% of all tuberculosis cases (Nene et al., 2019; WHO, 2022). Moreover, tuberculosis is a key disease for prevention and control in China, and its treatment is already covered by medical insurance (National Disease Control and Prevention Administration, 2023; National Disease Control and Prevention Administration, 2024; National Healthcare Security Administration, 2024).

Therefore, this study is feasible and profoundly significance. The outcomes of this study have the potential to significantly influence clinical practice by providing robust evidence on the viability of a shorter, more convenient treatment option for spinal tuberculosis.
